## Abstract

A new double-chamber syringe (DUO Syringe) was developed for intravenous drug administration and catheter flushing. This study presents a protocol for pre-clinical usability tests to validate the golden prototype of this new device, performed in a high-fidelity simulation lab by nurses. A two-steps parallel randomized controlled trial with two arms was designed (with standard syringes currently used in clinical practice and with the DUO Syringe). After randomization, eligible and consented participants will be requested to perform, individually, intravenous drug administration and flushing, following the arm that has been allocated. The procedure will be video-recorded for posterior analyses. After the completion of the tasks, nurses will be asked to answer a demographic survey, as well as an interview about their qualitative assessment of the device. A final focus group with all participants will also be conducted. Primary outcomes will concern the DUO Syringe’s effectiveness, efficiency, and safety, while secondary outcomes will focus on nurses’ satisfaction and intention of use. The pre-clinical protocol was defined according to the legal requirements and ISO norms and was reviewed and approved by the Ethics Committee of the Health Sciences Research Unit: Nursing of the Nursing School of Coimbra.

## 1. Introduction

Peripheral intravenous catheterization is the most common medical procedure performed by nurses, enabling the administration of intravenous solutions. This invasive practice is frequently associated with several complications (e.g., phlebitis, bloodstream infection, dislodgment, obstruction), leading to premature catheter replacement. Peripheral intravenous catheter (PIVC) related complications increase the length of hospital stay and, subsequently, healthcare costs [1]. Current complication rates can be decreased through preventive practices, especially PIVC flushing. This technique consists of rinsing the PIVC before and after its use [2]. Flushing not only maintains PIVC patency but also prevents the mixing of incompatible drugs/solutions [2]. Several studies showed that PIVC flushing removes blood and drug sediments from the catheter’s lumen, which potentiates catheter obstruction and bacterial colonization [3,4,5]. Considering international recommendations, to accurately administer intravenous drugs, nurses should flush the catheter pre, post, and between each drug administration, requiring at least two syringes. Despite the high level of policy awareness, nurses do not always follow international best practice recommendations regarding flushing practices [6,7]. To overcome this, prefilled flush syringes and multi-chamber syringes have been developed and distributed in international markets. Nevertheless, the use of prefilled syringes across international settings is minimal [8] and the need to use the same two syringes remains. Some double-chamber syringes were developed for drug reconstitution to promote faster drug administration by presenting a chamber with a prefilled drug in liquid or lyophilized form while maintaining sterility [9]. Others enable the delivery of two fluids in two moments, with a prefilled flush solution chamber and an empty chamber to be filled with the drug component [10]. However, current double-chamber syringes do not accomplish the international guidelines on infusion nursing, because they only enable the administration of the flush solution after drug delivery (the flush solution chamber can only be used after the drug chamber is empty) and do not accomplish the patency assessment of the PIVC [11].

Facing this, the goal of our project is to develop a new medical device that allows nurses to conduct intravenous drug administration and catheter flushing using only one double-chamber syringe. This new device is a double-chamber syringe that can be filled with a flush solution and intravenous drug, without mixing them, and allow for the delivery of each fluid separately (in equal or different volumes), enabling the assessment of the catheter patency through the administration of flush solution, drug delivery, and a final flushing of the catheter using the remaining flush solution.

The development of medical devices has vastly increased over the last decade, presenting an important role in clinical practice by improving patients’ well-being and quality of life [12]. Given the insurgence of new devices, the transition between prototype development and its implementation into clinical practice requires strict assessment and regulation. Contrasting pharmaceuticals, medical devices do not have straight or explicit regulations to follow [13], with regulatory directives diverging between countries. To bridge this gap, an international volunteer group of regulators was created (International Medical Device Regulators Forum; IMDRF), based on the work of the Global Harmonization Task Force on Medical Devices (GHTF) [14], specifically to uniform the regulatory directives around the world. In the European Union (EU), a new Regulation 2017/745 (5 April 2017) was recently approved by the European Parliament and the Council on medical devices [15]. Moreover, the development and implementation of new devices must be conducted under established standards, defined, and published by the International Organization for Standardization (ISO), striving for product quality, safety, and efficiency [16,17,18,19,20,21]. The development of international recommendations highlights the need to integrate the Health Technology Assessment (HTA) core assumptions in the development of new medical devices. In fact, 2.5% of all security events in NSW Health had a medical device as the main responsible cause. In 2014, 4000 incidents were reported (from near-miss until the death of the patient), involving four categories of high-risk devices: volume infusion pumps, infusion syringes, patient-controlled analgesia pumps, and defibrillators. More than 80% of the clinical incidents involving these devices can be attributed to errors in use requiring usability test [22,23,24,25].

Usability is defined in ANSI/AAMI/IEC 62366-1 as “the extent to which a user can use a product to achieve goals with effectiveness, efficiency, and satisfaction in a specific context” [19]. Notwithstanding, the technical report AAMI/IEC/TIR 62366-2 presents a broader focus of usability, highlighting the importance of assessing medical devices’ task accuracy, completeness, and efficiency, as well as user satisfaction [20]. According to these international directives, the medical devices’ development process comprises several strict and sequential stages, to predict potential errors carried out by end users and prevent the risk of use error due to the ergonomic features of the device. The pre-clinical validation of several parameters related to ergonomic, usability, and human factors is required to ensure that the prototype meets all the requirements to move forward to clinical studies [17,18]. Thus, the purpose of this study is to present the usability validation protocol for a double-chamber syringe supported in the user-centered design (UCD) method [26,27,28]. Specifically, we aim to describe the pre-clinical validation steps that will be used during the assessment of the functional prototype to accomplish the requirements established by the regulatory entities. This study protocol was developed under the SPIRIT 2013 Guidelines [29], with some adjustments according to pre-clinical trials in healthcare simulation research specificities [30,31].

## 2. Materials and Methods

### 2.1. Study Design

A two-steps parallel randomized controlled trial (RCT, Figure 1) with two arms was designed (involving standard syringes currently used in clinical practice and the new double-chamber syringe), following the Consolidated Standards of Reporting Trials (CONSORT) 2010 recommendations [28,29,30]. Considering that this project comprises the development of a new medical device, the EU directives [15], implemented in Portugal by the Portuguese National Authority of Medicines and Health Products (INFARMED), and ISO Standards [16,17,18,19,20] were considered. The pre-clinical study is planned to last 3 months from the start of the recruitment process (in July 2020).

### 2.2. Participants Recruitment and Sample Size

The research team will send an invitation to the intended users for this medical device, namely nurses from local tertiary hospitals to participate in the study. All interested nurses will be screened for eligibility criteria (Table 1). Regarding sample size, around 15–25 participants are usually considered to enroll in the usability tests, 15 being the acceptable minimum number according to the regulatory entities of the USA [26]. Although in the EU these parameters are not well-established, the U.S. Food and Drug Administration’s (FDA) orientation guidelines for medical devices highlight the need to balance the heterogeneity and homogeneity of the samples, reflecting as much as possible the target population [27]. For the usability tests with the double-chamber syringe, the AAMI/IEC/TIR 62366-2 was used to accomplish the sample size determination. According to that standard, there are diminishing returns on detecting new usability problems when sample size goes beyond 10 for each distinct user group. This is based on calculations determining cumulative probability of detecting a usability problem: R = 1 − (1 − P)^n^, where R equals the cumulative probability of detecting a usability problem, P equals the probability of a single test showing a usability problem, and n equals number of participants [20]. Therefore, 10 nurses will be enrolled in each arm (20 for each phase of this study), in a total of 40 participants in overall pre-clinical usability testing. The participants will not be compensated for participation.

### 2.3. Patient and Public Involvement

No patients or participants from the general public will be involved in this trial.

### 2.4. Randomization and Blinding

Eligible and consenting participants will be randomly allocated to one of two arms (Figure 1) for each phase of the study, using simple randomization (1:1 ratio). Random allocations through random number sequences will be computer-generated through an online registration system (Sealed Envelope^TM^, London, England). To ensure allocation concealment, the study staff will randomize each participant unknowingly and informed the principal investigator. Considering the specificities of this device, both of the two steps of the RCT will not be blinded, since it consists of the use of different devices to conduct the experiments of each allocated arm. Despite this, the participants will not be directly informed of their group allocation and will only be informed about the broad purposes of the research and the specific tasks they need to accomplish in the usability test.

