### 2.6. Interventions

This pre-clinical validation will be assessed through a two-arm parallel RCT in two phases (Figure 1), in which the nurses will be requested to perform intravenous drug administration per the allocated arm in the simulated setting. In order to ensure the standardized conditions for the procedure, the PIVC is already in place (being placed always by the same nurse of the research team). In the first phase (intra-subject analyses), the 20 nurses will perform the protocol using the two types of syringes, starting with the double-chamber syringe and, then, a standard syringe (arm A), or in reversed order (arm B). In the second phase (inter-subject analysis), another 20 nurses (without any previous information or contact with this double-chamber syringe) will be allocated to perform the protocol with a double-chamber syringe (arm A) or with standard syringes (arm B). The usability test session will be run as a single participant test, with each participant repeating the procedure three times, under external supervision. The procedure is divided in two main phases (drug preparation and drug administration), and tasks were defined in accordance to both study groups (Table 3 and Table 4). The procedure will be recorded by audio/video for posterior analyses. At the end of the usability tests, interviews/focus group with all participants will be conducted to collect detailed qualitative information about this new medical device.

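### Simple randomization cannot guarantee the 10 nurses per arm that the sample size section states for each phase

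*Protocol article*

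**What the plan says.** Section 2.2 of the protocol article fixes the arm size: "10 nurses will be enrolled in each arm (20 for each phase of this study"). It puts the sum over both phases at 40. It bases the 10 on a problem-detection formula, R = 1 − (1 − P)^n, and on a cited standard under which "there are diminishing returns on detecting new usability problems when sample size goes beyond 10 for each distinct user group". It gives no value for P or R.

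Section 2.4 fixes the mechanism. Nurses are "randomly allocated to one of two arms (Figure 1) for each phase of the study". The method it names for this is allocation "using simple randomization (1:1 ratio"). On the source of the sequence it says: "Random allocations through random number sequences will be computer-generated through an online registration system". The section states no block, stratum, cap per arm or replacement rule, and it says that both steps are unblinded.

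Section 2.6 gives the arms different meanings in the two phases. In Phase 1 "the 20 nurses will perform the protocol using the two types of syringes", so the arm is the order of use. In Phase 2 another 20 nurses "will be allocated to perform the protocol with a double-chamber syringe (arm A) or with standard syringes (arm B"), so the arm is the device.

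**The concern.** A fixed total of 20, a fixed 10 per arm and unrestricted allocation cannot all be assured together. Under simple randomization the arm size is a random quantity, and the sample size section treats it as known.

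Two things are at stake.

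- **Phase 2.** The number of double-chamber users is the n of the detection formula for that phase, and it may fall short of 10.
- **Phase 1.** The order groups may be unequal. Section 2.7 expects a learning curve over repeated procedures, and section 2.8 lists paired tests. In a plain paired comparison, a learning or other period effect cancels only when the two orders are equally frequent.

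This is not a detail left to a fuller document. The article names both the method and the arm size, and the two do not fit.

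**Working it through.** **The plan's own figure.** 10 per arm × 2 arms = 20 per phase; 20 × 2 phases = 40. The total is consistent. The 10 itself cannot be re-derived, because section 2.2 gives neither P nor R.

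**Inputs.** 20 nurses per phase (sections 2.2 and 2.6), simple 1:1 allocation, and separate randomization in each phase (section 2.4). The number in arm A is then X ~ Binomial(20, 0.5).

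**Exact balance.**
- One phase: P(X = 10) = C(20,10)/2^20 = 184756/1048576 = 0.176.
- Both phases: 0.1762² = 0.031.

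**Size of the imbalance in either direction, per phase.**
- 13:7 or worse: 2 × P(X ≤ 7) = 2 × 137980/1048576 = 0.263.
- 14:6 or worse: 2 × P(X ≤ 6) = 2 × 60460/1048576 = 0.115.
- Expected absolute difference between arms: 3.52 nurses. The expected smaller arm is 10 − 3.52/2 = 8.24.

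**Phase 2, double-chamber arm only (one tail).**
- P(X ≤ 9) = 431910/1048576 = 0.412.
- P(X ≤ 7) = 137980/1048576 = 0.132.

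**Detection in Phase 2 taken alone.** R = 1 − (1 − P)^n. The values of P are assumptions, since the document gives none.

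| Assumed P | R at n = 10 | R at n = 7 |
|---|---|---|
| 0.10 | 0.651 | 0.522 |
| 0.15 | 0.803 | 0.679 |
| 0.20 | 0.893 | 0.790 |
| 0.30 | 0.972 | 0.918 |

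**Phase 1, effect of unequal orders.** Let τ be the true difference, double-chamber minus standard, and d the period effect, second use minus first. A nurse in arm A (double-chamber first) contributes τ − d, and a nurse in arm B contributes τ + d. The mean over 20 nurses is τ + d(nB − nA)/20. The shift has absolute size d × |nA − nB|/20:
- at 10:10: 0;
- at the expected imbalance: 3.52/20 = 0.18d;
- at 13:7: 6/20 = 0.3d.

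**Loss of precision in the Phase 2 comparison.** Efficiency relative to 10:10 is 4·nA·nB/20²: 0.96 at 12:8, 0.91 at 13:7 and 0.84 at 14:6.

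**Recruiting on until both arms hold at least 10.** After 20 nurses the mean shortfall in the smaller arm is 3.52/2 = 1.76. Each missing nurse takes 2 further randomizations on average, so the expected total is 20 + 2 × 1.76 = 23.5 nurses per phase.

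**The case against.** The case on the other side is substantial, and most of it limits the size of the point.

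- **The arm size may be a planning number.** Simple randomization is a valid method, 10:10 does occur in 17.6% of single phases, and an 11:9 split is harmless. A reader might infer that the stated sizes are unattainable. The documents support only that they are not guaranteed.
- **The word simple may be loose for a balanced list.** Figure 1, cited in the same sentence, is not shown. This lowers confidence about what will be done, but the text as written would then still need correcting.
- **Detection over the whole study barely moves.** All 20 Phase 1 nurses use the double-chamber syringe. With 7 in Phase 2 there are 27 users in place of 30. At an assumed P of 0.15, R is 1 − 0.85^27 = 0.988 against 1 − 0.85^30 = 0.992. The losses in the table apply only when Phase 2 is read alone. Section 2.2 also speaks of diminishing returns beyond 10 and does not call 10 a minimum. This stands.
- **The Phase 1 shift is not bias in the usual sense.** It averages to zero over randomizations. It is error conditional on the split that actually occurs, and an analysis with a period term would remove it. This stands too.
- **Staff balancing the arms by hand.** A reader might expect the last nurses to be steered into the smaller arm. Nothing in section 2.4 describes this; allocation is computer-generated. It is no part of the point.

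What survives is the mismatch between the two sections, and its avoidable consequences in each phase.

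**Conclusion.** The point holds as a real, moderate and easily removed inconsistency. Sections 2.2 and 2.4 together state an arm size that the named method secures in both phases only 3.1% of the time. The stricter figure counts small imbalances as failures; the more telling one is that 26% of phases would split 13:7 or worse.

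The practical effect lies mainly in Phase 2, where the double-chamber arm has 7 or fewer nurses with probability 0.13. The 0.26 refers to either arm and should not be read as the risk to the double-chamber arm. In Phase 1 the effect is confined to the order of use.

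The results assume exactly 20 nurses randomized per phase, independent allocation with probability 0.5, and separate randomization of the phases. The detection figures rest further on the assumed P of 0.10 to 0.30, and the Phase 1 figure on a paired comparison without period adjustment. The documents do not support calling the trial invalid or its estimates systematically biased.

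**What to change.** In section 2.4, replace simple randomization with restricted 1:1 randomization done separately within each phase. The preferred form is a concealed, computer-generated random permutation of 10 A and 10 B. Larger permuted blocks of varying, undisclosed size that sum to 20 are an alternative. Small blocks of 2 and 4 are less suitable, because staff who see past allocations in an unblinded trial could often work out the next one.

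Either form gives 10:10 once all 20 nurses of a phase are randomized. It secures the number randomized, not the number completing, since section 2.9 allows withdrawal.

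The cost is one phrase and a different list type, with no extra nurses. The downside is that the last allocations become partly predictable to anyone who keeps a tally, so the list should be held away from staff who enrol.

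If simple randomization is kept, section 2.2 should state 10 per arm as an expected number and accept unequal arms.

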### 2.5. Materials

The usability tests will be conducted in a laboratory environment that simulates two areas commonly found in hospital wards: (i) a fully equipped treatment room, where nurses commonly prepare intravenous drugs; (ii) a fully equipped single-bed patient room. Both areas contain audio/video recording equipment, allowing for a panel of evaluators to follow the tests in real time, without direct interaction with the participants, and for posterior analyses. The tests will be performed using an upper arm simulator that allows for PIVC insertion and drug administration (Multi-Venous IV Training Arm Kit; Nasco Healthcare, Fort Atkinson, WI, USA). This is a lifelike adult arm reproduction with a multi-vein system designed for peripheral intravenous therapy in the antecubital fossa or dorsum of the hand, with median, basilic, and cephalic accessible and palpable veins that allow intravenous peripheral therapy simulation (Figure 2). The study protocol ensures that all participants received standardized instructions and materials to perform the usability test.

The double-chamber syringe was developed with a 20 mL size: 10 mL for drug chamber (blue plunger) and 10 mL for flush solution chamber (white plunger). This innovative double-chamber syringe enables the filling (none of the chambers are pre-filled) and administration of both solutions (verification of the catheter patency through the administration of the flush solution, the subsequent drugs delivery, and the final flushing of the catheter using the remaining flush solution) [32]. With the double-chamber syringe, the instructions for use will be provided to the participants, which will be also assessed by the participants in the interviews/focus groups.

Supplementary materials will be used, such as (i) the informed consent document, with a brief description of the study, the main purpose of the groups, and the voluntary nature of participation; (ii) non-disclosure agreement (NDA); (iii) anonymous demographic questionnaire to sample characterization; (iv) interviews and focus groups guidelines (Table 2); and (v) usability questionnaire (42 items in a 7-point Likert scale focused on significant usability dimensions: usefulness, ease of use, ease of learning, satisfaction, and intention to use).

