### 2.7. Outcomes

These usability tests are intended to measure primary (effectiveness, efficiency, and safety) and secondary outcomes (satisfaction and intention of use), ensuring that the medical device accomplishes the needed legal requirements before testing in real clinical settings. Specifically, in this pre-clinical study, the primary outcomes that will be measured are: (i) number of tasks and goals achieved; (ii) procedure execution time; and (iii) number, type, and intensity of errors (Table 5). These parameters will be extracted from the video recordings (usability tests) and compared to a detailed procedure checklist. The secondary outcomes will be assessed through the usability questionnaire and audio recordings from the individual interviews and focus group carried. As the participants perform each procedure three times (with the double-chamber syringe and standard syringes), the research team can also analyze their learning curve and training needs required to use this new medical device, along with the qualitative (interviews and focus group) and quantitative (usability questionnaire).

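### The reason given for no blinding covers only the visible device; raters of the recordings could still be masked to run number and, in Phase 1, to order of use

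*Protocol article*

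**What the plan says.** Section 2.4 (Randomization and Blinding) states that "both of the two steps of the RCT will not be blinded, since it consists of the use of different devices to conduct the experiments". It gives no other reason. It then adds a partial safeguard on the participants' side: "the participants will not be directly informed of their group allocation".

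Section 2.5 (Materials) describes recording equipment "allowing for a panel of evaluators to follow the tests in real time, without direct interaction with the participants, and for posterior analyses".

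Section 2.7 (Outcomes) includes among the primary outcomes the "number, type, and intensity of errors", and says how the primary outcomes are obtained: "These parameters will be extracted from the video recordings (usability tests) and compared to a detailed procedure checklist". It adds that, because the procedure is performed three times, "the research team can also analyze their learning curve and training needs required to use this new medical device".

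Section 2.6 (Interventions) defines the arms. In Phase 1 all 20 nurses use both kinds of syringe, and arms A and B differ only in which comes first. In Phase 2 another 20 nurses use one kind each, and the arms differ by device.

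**The concern.** The decision is broader than the reason offered for it. That the devices look different explains why a rater cannot be masked to the device. It does not explain why a rater must know the run number, or the order in which a Phase 1 nurse used the two syringes. Both can be withheld from someone who scores a recording.

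Two contrasts are exposed. The learning curve rests on differences between runs 1, 2 and 3. All nurses go through the runs in the same order, so randomisation cannot balance a rater's expectation that later runs will be better. In Phase 1 the randomised groups are the two orders, and section 2.8 plans to compare the groups within each study phase. Leniency or severity towards whichever syringe came second would enter that comparison.

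The outcome leaves room for this. The intensity of an error is a matter of degree, and several items in Table 5 (compliance with aseptic technique, compliance with push–pause flushing) need a rater's judgement.

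**Working it through.** **1. Does the stated reason reach each feature that could be masked?**

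| Feature | Need a single-run clip reveal it? | Covered by the reason in section 2.4? |
|---|---|---|
| Device | Yes, the syringe is visible | Yes |
| Phase 2 arm | Yes, arm = device | Yes |
| Phase 1 arm | No, arm = order, and both arms use both devices | No |
| Run number (1, 2, 3) | No | No |

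**2. How many recordings are involved?** The inputs are 10 nurses per arm and 20 per phase (section 2.2), and three repetitions (sections 2.6 and 2.7). The plan's total reproduces: 10 × 2 arms × 2 phases = 40 nurses.

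- Phase 1, three runs per device: 20 × 2 × 3 = 120.
- Phase 2: 20 × 1 × 3 = 60.
- Total: 120 + 60 = 180.
- If a Phase 1 nurse does only three runs in all: 20 × 3 + 60 = 120.

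This is the reach of the issue, not the size of a bias.

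**3. Where would rater expectation go?** Suppose raters mark run 3 more gently than run 1 by an amount m, and the second-used syringe more gently than the first by an amount s, equally for both devices.

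- Learning curve: observed fall in errors from run 1 to run 3 = true fall + m. Every nurse has the same run order, so m does not average out.
- Phase 1, same device compared between arms (used first against used second): observed difference = true difference + s.
- Phase 1, within-nurse device difference (double-chamber minus standard), with true value d: arm A, where the standard syringe comes second, gives d + s; arm B gives d − s. With 10 per arm the mean is [10(d + s) + 10(d − s)] / 20 = d, so s cancels. With unequal arms of sizes a and b, s(a − b)/(a + b) is left over.
- Phase 2, device difference: m applies to both arms and cancels.

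**4. Illustration of direction (assumed bias).** The article gives neither a standard deviation nor a bias size, and names no test for run 1 against run 3. Assume no true learning, a paired t-test at two-sided 0.05, and a rating shift of b standard deviations of the within-nurse difference. The rejection rate follows from the noncentral t distribution with noncentrality b√n and n − 1 degrees of freedom.

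| b (assumed) | b√20 | Rejects, n = 20 | b√10 | Rejects, n = 10 |
|---|---|---|---|---|
| 0 | 0 | 5.0% | 0 | 5.0% |
| 0.1 | 0.447 | 7.1% | 0.316 | 5.9% |
| 0.2 | 0.894 | 13.6% | 0.632 | 8.8% |
| 0.3 | 1.342 | 24.7% | 0.949 | 13.6% |
| 0.5 | 2.236 | 56.5% | 1.581 | 29.3% |

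Here n = 20 is one device in Phase 1 and n = 10 is one device in Phase 2. The table shows the direction and a range. It does not estimate what will happen in this trial.

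**The case against.** A reader might infer from section 2.5 that the panel watching live, in sequence, also assigns the error grades and therefore knows each run's place. The article does not say so. It says the equipment makes live viewing possible, and section 2.7 takes the primary outcomes from the recordings against a checklist. Who scores, and in what order, is not stated. The route to bias is therefore unguarded rather than documented.

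A reader might also say that blinding has been abandoned altogether. That is too strong, since participants are not directly told their group. The gap is on the raters' side.

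Clip handling is, moreover, an operational detail that a condensed article may leave to a fuller document. That holds for the details. It does not hold for section 2.4 itself, which states that neither step is blinded and gives a reason that does not fit the Phase 1 arms.

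The learning curve is something the team may analyse in addition, not a named primary outcome. Many Table 5 items are concrete events, such as the wrong chamber, a volume in mL or accidental catheter removal, and a checklist limits discretion. Equal leniency by run or order also largely cancels from the device comparisons, as shown above. All of this stands and limits the importance of the point. It leaves the run and Phase 1 order contrasts, and the items that do need judgement, unprotected.

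**Conclusion.** The point holds in a limited form. The reason in section 2.4 justifies leaving raters unmasked to the device. It does not justify leaving them unmasked to run number or, in Phase 1, to order of use, which is the randomised arm there. The contrasts at risk are the learning curve and the Phase 1 order comparison, for the judgement-based error outcomes.

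The size of any bias is unknown. It depends on whether raters know the sequence and whether that knowledge shifts their grades, and the article settles neither. It would be wrong to conclude that the device comparisons are invalid, or that this masking would rid them of detection bias. Bias from seeing the device stays in both phases whatever is done about run and order. Execution time leaves little to judgement and is little affected. No figure in the plan changes. Because the masking is cheap and can be applied after the sessions are recorded, it is worth adopting.

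**What to change.** Reword section 2.4 along these lines: unblinded to device; raters of the recordings masked to run number and, in Phase 1, to order of use.

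To carry this out, cut each session into single-run clips, give each a random code, remove run and sequence labels, and score tasks and errors from these clips in random order across nurses, runs and periods. Where possible, assign each clip to team members who did not watch that session live.

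The cost is clip preparation, a coding list and some care in assigning scorers, for at most 180 clips. The sessions, participants and equipment stay the same. Some clips may still show clues to order, so the masking will be imperfect.
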